### Procedure

We will recruit patients during urological consultations and after diagnosis of localized prostate cancer. Men who meet the inclusion criteria will receive detailed information about the study. In particular, the aims, methods and intension of setup a bio-bank will be fully explained and written informed consent will be obtained. Data and samples (prostate tissue, blood and urine) will be acquired during the routine consultation before, during and after the treatment. The follow up point of times are usually three, six and twelve month after treatment, then annually. Assistance by study nurses will ensure a mostly complete data acquisition. An overview of the study flow during the first three years is illustrated in figure 1. Unexpected events between the routine controls will be recorded and followed. Within the quality control all acquired data will become controlled before input into the central data base will take place. A reversible anonymization for all samples belonging to the bio-bank will be performed. In a preliminary phase of the study we will translate and validate the EPIC (Expanded Prostate Cancer Index Composite) questionnaire into German language to have a mostly precise instrument for assessing disease specific quality of life and especially changes in quality of life.

**Figure 1 F1:**
[figure not shown]
Study flow (the first three years).

### Kind of collected data and samples

• Clinical data including quality of life and lifestyle factors. For general quality of life assessment we use SF-36v2 questionnaire and a "Feeling Thermometer", a valid and reliable global estimate of health-related quality of life. For prostate cancer specific quality of life we will use the EPIC questionnaire (Expanded Prostate cancer Index Composite) and the IPSS (International Prostate Symptoms Score). In a preliminary phase of the study we will perform a translation and validation of the EPIC questionnaire into German language.

• Prostate needle biopsy cores are already available due to preceded diagnosis and need only a special labeling. In case of prostatectomy as final treatment the whole organ will be stored, partly as formalin fixed and paraffin embedded specimen in the corresponding pathology unit of the hospital, where treatment is performed (multi-center storage), partly a shock frozen specimen in the central bio-bank of the Department of Pathology of the University Hospital of Zurich. The same procedure will be performed in case of repeated prostate needle biopsy.

• For the bio-bank we will acquire further one tube of whole blood, one tube of heparin full blood and two tubes of EDTA full blood, all of them as venous blood; further about 40 ml of native midstream urine. After anonymization these samples will be immediately send to the Clinical Chemistry of the University Hospital of Zurich, where aliquotation, DNA extraction, freezing and storage will take place.

### Outcome measures (baseline and follow up)

Data and samples acquired at diagnosis and before treatment belong to the baseline data. Data and samples acquired during the follow up and after the treatment belong to the follow up data. With exception of active surveillance as treatment or in case of suspicion of cancer recurrence, during the follow up no prostate tissue will be acquired routinely, whereas the clinical data and blood and urine samples for the bio-bank will be acquired at all the visits.

### Objectives

• To describe epidemiologic aspects of patients with newly diagnosed localized prostate cancer; in particular, to evaluate survival, functional outcomes, quality of life and life style in the context of treatment modality, prognosis and other clinical information.

• To assess the clinical relevance of recently proposed biomarkers.

• To develop individualized, science-based treatment recommendations for patients with localized prostate cancer.

• To link results from basic science to applied clinical research. For example, the study setup allows the investigation of promising prognostic genetic and post-genetic markers in a realistic clinical context and facilitates the translation of basic scientific discoveries into clinical practice and patient care.

• To provide a research platform for future diagnostic and prognostic markers using the systematically collected set of tissues and body fluids.

• To generate a German version of the EPIC questionnaire to get a validated instrument for assessment of quality of life in prostate cancer patients available for German speaking countries.

### Safety monitoring and adverse events

Any unexpected and/or adverse events will be recorded and followed until they have abated or until a stable situation has been reached. Treatments or interactions may necessary due to such events will take place within the urological or general physician's consultation.

### Ethics

This cohort study will be performed in accordance to the World Medical Association Declaration of Helsinki [14] and the guidelines of the Swiss Academy of Medical Sciences concerning scientific research involving human beings [15] and bio-banks [16] and will seek approval by the Ethical Committee of the Canton of Zurich. Further, all handling of personal data will strictly comply with the federal law of data protection of Switzerland (Bundesgesetz über den Datenschutz (DSG) vom 19. Juni 1992).

### Statistical analysis

Epidemiologic data and patients' descriptives available on continuous scales will be presented with medians, interquartile ranges or means and standard deviations as appropriate. Categorical data will be presented as rates and percentages.

Association of individual (independent) variables on the outcome variables will be reported using correlation coefficients. Results from univariate analysis will inform multivariate modeling.

Assessment of causal associations will be performed using multivariate models including potential confounders along with the independent variables of interest. Prognostic scores will be built using either multivariate logistic regression analysis or Cox proportional hazard models. Models will be validated in cross samples. Calibration and discrimination of the cross-validated prognostic instruments will be assessed using the Brier Score.

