The second problem concerns the selection of appropriate treatment. Adequate choice is difficult because the natural course of disease is often unknown and both patient and clinician face the challenging decision whether active treatment is justified. Indeed, some studies showed a reduction in mortality [9-11]. However, identification which of the available treatments is best for an individual patient remains controversial, particularly because quality of life data are only limited available. Trials in this field are currently in progress. The Veterans Affairs Prostate Cancer Intervention vs. Observation (PIVOT) trial compares radical prostatectomy versus observation in 731 men and will complete the follow-up in 2009. The ongoing UK Prostate Testing for Cancer and Treatment Study (ProtecT) will randomize men with prostate cancer to receive radiation, undergo radical prostatectomy, or remain in observation; this trial is nested within a superior PSA screening trial, and study accrual is estimated to be completed in 2008.

The goal in treating patients with localized prostate cancer is a curative one and includes minimizing adverse effects to preserve an adequate quality of life. Better understanding on how the quality of life is affected depending on the treatment modality – surgery, radiation, active surveillance or even a palliative transurethral resection of the prostate (TUR-P) – would be a first, important step by assisting patients in deciding which treatment to choose. An improvement in the knowledge concerning prognosis would be a further, mostly important step. Here, the development of prognostic biomarkers that indicate the future course of the illness is a promising approach with potential and the focus of much attention. A further topic of interest concerning the prognosis of prostate cancer and prostate cancer survivors is the influence of lifestyle factors, such as nutrition and physical activity. Patients cured from cancer die of non-cancer causes at a higher rate than the general population and co-morbid conditions are probably the result of cancer treatment, genetic predisposition and lifestyle factors [12]. Increasing the knowledge concerning these topics could be of precious help in optimizing treatment outcome.

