### Study sample size and duration

We performed a sample size calculation for survival endpoints based on the recommendation of Dupont and Plummer [13]. We have set the alpha error at 0.05 and the beta error at 0.2 and assumed a median survival time in the control group of 15 years. We specified a hazard ratio of the control group relative to the experimental group of 1.2, an accrual time during which patients are recruited of ten years and no additional follow-up time after end of recruitment. Since we are interested in various endpoints we chose an extreme ratio of control to experimental patients of 5 to be on the safe side. Based on these assumptions the required sample size is 1545. Given the size of the catchment's area we anticipate to include about two hundred new patients annually which lead to a sufficient number of patients to perform analyses after the end of the recruitment period.

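### Univariable associations are to be reported as correlation coefficients with no exemption for censored survival or for unordered treatment groups

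*Protocol article*

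**What the plan says.** The Statistical analysis section of the protocol article states: "Association of individual (independent) variables on the outcome variables will be reported using correlation coefficients". It does not limit this by type of outcome or type of explanatory variable. The next sentence gives the results a second use: "Results from univariate analysis will inform multivariate modeling".

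The outcomes and exposures concerned are set out elsewhere in the article:

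- The first objective is "to evaluate survival, functional outcomes, quality of life and life style in the context of treatment modality, prognosis and other clinical information".
- The sample size section confirms that time-to-event outcomes are central ("We performed a sample size calculation for survival endpoints") and assumes "an accrual time during which patients are recruited of ten years and no additional follow-up time after end of recruitment".
- The Background names four treatment modalities: radiation, surgery, palliative TUR-P and active surveillance. They have no natural order.

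The same Statistical analysis section assigns causal questions to multivariable models with confounders, without naming the model type. It assigns prognostic scores to logistic regression or Cox models.

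**The concern.** The sentence names a measure that does not suit survival, the outcome on which the study is sized. To correlate a covariate with survival, an analyst would need a fully observed number for each man. The two obvious candidates are observed follow-up time and death yes/no. Both ignore that men enter over ten years and so are observed for different lengths of time.

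Two things follow. Real prognostic effects are diluted, because most of the spread in observed time is spread in entry date. A covariate with no effect on survival can also look associated if its level changes over the accrual period, since late entrants have short follow-up whatever their prognosis.

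For treatment modality the difficulty is different. If four unordered groups are coded as integers, the coefficient depends on which group receives which number.

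These results would be reported in their own right and would inform the multivariable models. A misleading univariable result could therefore reach readers directly or influence which variables are carried forward.

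**Working it through.** **Inputs from the sample size section.** Control median survival 15 years; hazard ratio 1.2, control relative to experimental; accrual A = 10 years; additional follow-up F = 0; five controls per experimental patient; alpha 0.05; power 0.80; about 200 men a year, so 200 × 10 = 2,000. Exponential survival and uniform entry are my assumptions.

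**Check that the inputs are read correctly.** The experimental median is 15 × 1.2 = 18 years, and the average median is (15 + 18)/2 = 16.5. The event probability at that median is

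p = 1 - (1 - exp(-λA))/(λA), with λ = ln 2/16.5 = 0.0420, so p = 0.1835.

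Then n = (1.960 + 0.842)² × (1 + 1/5) / ((ln 1.2)² × 0.1835) = 1544.3, which rounds up to the stated 1545. In this formula n is the experimental group size. That is a separate matter; here it shows only that the survival and follow-up assumptions are read as the article used them.

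**Extent of censoring.** For the control median, λ = ln 2/15 = 0.0462 and λA = 0.462, so p = 1 - (1 - 0.630)/0.462 = 0.199. For the 18-year median, p = 0.170. About 80% of survival times are therefore censored, each at 10 years minus entry time.

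**Dilution of a real effect.** I simulated 1,000,000 men with a normally distributed marker, hazard ratio 1.2 per SD and no drift. Spearman r is -0.15 with true survival time and about -0.04 with observed time. With death yes/no, |r| is about 0.08.

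**Spurious association.** Here the marker has no effect on survival, but its mean shifts over accrual. N = 2,000. The documents give no drift size, so a range is shown. The entries are the percentage of cohorts significant at a nominal 5%.

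| Drift over accrual (assumed) | Observed time, F = 0 | Death yes/no, F = 0 | Observed time, F = 5 years (assumed) |
|---|---|---|---|
| none | about 5% | about 5% | about 5% |
| 0.1 SD | 17% | 6% | 9% |
| 0.25 SD | 71% | 14% | 36% |
| 0.5 SD | over 99% | 37-40% | 89% |

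Hand check for the 0.25 SD row, observed time, F = 0: r = -0.057, so |z| ≈ 0.057 × √2000 = 2.55 and P(Z > 1.96 - 2.55) = 0.72, in line with 71%.

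With F = 5 the event probability rises to 1 - (exp(-0.231) - exp(-0.693))/0.462 = 0.36.

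**Comparison with Cox.** A binary null covariate whose prevalence drifts by an assumed 20 percentage points, N = 2,000, F = 0: r with observed time is about -0.10 and significant in 99% of cohorts. Death yes/no is significant in 23%. A univariable Cox model on the same data is significant in 5%, with a mean log hazard ratio near 0.

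**Treatment coding.** Four groups with illustrative means of 70, 60, 80 and 65 and SD 15: over all ways of numbering the groups 0 to 3, Pearson r runs from -0.45 to +0.45 on the same data.

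**The case against.** Three stronger conclusions are tempting, and the article does not support them.

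- *That correlation is wrong for every outcome.* The text refers to the outcome variables without an exception, but it does not say "all". The named instruments (SF-36v2, the Feeling Thermometer, EPIC, IPSS) give continuous or ordinal scores, for which a correlation is a reasonable summary.
- *That any drifting marker will appear related to survival.* Without drift the error rate is nominal. With 0.1 SD drift and death yes/no it is close to nominal. The 71% figure needs an assumed 0.25 SD drift, observed time as the variable, and no follow-up after accrual. That last condition is a sample size assumption: the Abstract gives a duration of at least ten years, and the Procedure section plans annual visits with no stated end.
- *That a correlation with treatment has no meaning.* Indicator coding of each modality gives interpretable point-biserial coefficients, and the article does not prescribe integer codes. The ±0.45 range applies only to integer coding and to the illustrative means.

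It can also be said that the correlations are only a first step. Causal claims go to multivariable models, Cox is available, and no selection by correlation p-value is stated. This lessens the defect, but part of it stands. Cox is named only as one of two options for prognostic scores, the causal models are not specified, and the correlations are both reported and used to inform modelling.

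Condensing for a journal explains missing detail. It does not explain an unrestricted sentence that names an unsuitable measure.

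**Conclusion.** The concern holds in a limited form. As written, the sentence applies correlation coefficients to survival and to treatment modality without exemption, and for censored survival that is the wrong measure.

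The dilution needs no drift: under the article's own assumptions, r on observed time is about a quarter of its value on true survival time (0.04/0.15). The spurious association is conditional. Its size depends on an assumed drift, on which survival variable is correlated, and on how long follow-up continues; for 0.25 SD drift and 2,000 men the three cases examined give 71%, 36% and 14%, against 5% with no drift. None of these is a forecast for this cohort. The coding problem arises only if a single coefficient is computed on integer-coded treatment.

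The defect lies in the univariable step and does not by itself invalidate the later models. It should be corrected before analysis.

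**What to change.** Replace the sentence with one that matches the measure to the variable type:

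- Correlation coefficients only for pairs of continuous or ordinal, fully observed variables, such as quality-of-life and symptom scores.
- Univariable Cox hazard ratios, or Kaplan-Meier or cumulative incidence estimates, with 95% confidence intervals for time-to-event outcomes.
- Group differences with 95% confidence intervals for comparisons by treatment modality.

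The cost is wording only. No additional data, visits or patients are needed.

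### Univariate associations are allowed to steer the multivariable models, with no link to the validation step and no exemption for confounders

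*Protocol article*

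**What the plan says.** All of the relevant text is in the Statistical analysis section of the protocol article, in this order.

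- Univariate step: "Association of individual (independent) variables on the outcome variables will be reported using correlation coefficients", followed directly by "Results from univariate analysis will inform multivariate modeling".
- Causal models: "Assessment of causal associations will be performed using multivariate models including potential confounders along with the independent variables of interest".
- Prognostic scores: "Prognostic scores will be built using either multivariate logistic regression analysis or Cox proportional hazard models".
- Validation: "Models will be validated in cross samples", and "Calibration and discrimination of the cross-validated prognostic instruments will be assessed using the Brier Score".

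The section gives no selection rule or p-value cut-off and no source for the list of confounders. It does not say whether the univariate step is done on all men or separately in each training sample. The Objectives section makes the stakes plain: it plans to assess proposed biomarkers, to study genetic and post-genetic prognostic markers, and to arrive at individual treatment recommendations.

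**The concern.** The one data-driven basis for model building that the plan names is each variable's marginal association with the outcome. It comes before two different kinds of model and excuses neither.

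**Prognostic scores.** Suppose markers are screened on all men and only the resulting model is cross-validated. The held-out men have then already helped to choose the predictors, and cross-validation cannot remove that part of the optimism. A score made of noise can appear to have been validated.

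**Causal models.** Whether a variable confounds depends on its joint relation with treatment and outcome. Its univariate relation with the outcome is the wrong criterion. A weak confounder can fail a screen by chance, and a masked one can fail because the treatment effect hides it. Treatment in this cohort is not randomised, so adjustment has to carry the comparison.

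**Working it through.** The plan states no figure on this point to reproduce. The check asks how large the effect would be if the sentence were applied as a filter.

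**Inputs from the article (Study sample size and duration).** The design "assumed a median survival time in the control group of 15 years", with a hazard ratio of 1.2, a 5:1 group ratio, ten years of accrual and no added follow-up. About 200 men a year for ten years gives N = 2,000. The stated requirement of 1545 serves only as an alternative N; whether it follows from its own inputs is a separate matter.

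**Assumed, not in the documents.** The number of candidate markers K, a screen at p<0.05, 10-fold validation, and the confounder strengths.

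**1. Event fraction.** With exponential survival and uniform entry over A = 10 years, P(event) = 1 − (1 − e^(−λA))/(λA), where λ = ln 2/median.
- Median 15 years: λA = 0.462, P = 0.199.
- Median 15 × 1.2 = 18 years: λA = 0.385, P = 0.170.
- Weighted 5:1: (5 × 0.199 + 0.170)/6 = 0.194, or about 389 events in 2,000 men.

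**2. Rough size by hand.** About m = 0.05 × K noise markers pass the screen. For a marker that passes, E[z² given |z|>1.96] = 1 + 2 × 1.96 × 0.0584/0.05 = 5.58. The excess over 1, which is 4.58, comes from selection on all men and so carries into the held-out men. With w = 1/389 + 1/1611 = 0.00319, a normal approximation for independent markers gives AUC ≈ Φ(4.58mw/√(2 × 5.58mw)).
- K = 50, m = 2.5: 0.0365/√0.0890 = 0.122, AUC ≈ 0.55.
- K = 200, m = 10: 0.146/√0.356 = 0.245, AUC ≈ 0.60.
- K = 10: no marker passes in 0.95^10 = 60% of data sets, so the average stays close to 0.50.

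**3. Simulation, N = 2,000, pure-noise markers (true AUC 0.50).**

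| Candidates | AUC, screen once on all men | AUC, screen inside folds |
|---|---|---|
| 10 | 0.51 | about 0.50 |
| 50 | 0.55 | about 0.50 |
| 200 | 0.60 | about 0.50 |

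A separate simulation at N = 1545 gives 0.54 against 0.49 with 50 candidates, 0.60 against 0.50 with 200, and 0.71 against 0.50 with 1000. With 10 candidates it gives 0.48 against 0.46. It pools predictions over folds, which puts the AUC for noise slightly below 0.50, so the difference is what counts.

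**4. The plan's own measure.** The scaled Brier score is 1 minus the ratio of the Brier score to that of predicting the overall event rate for everyone; zero means no skill. Screening outside against inside the folds:
- 10 candidates, N = 1545: −0.001 against −0.004.
- 50 candidates, N = 1545: +0.004 against −0.011.
- 200 candidates, N = 2,000: +0.017 against −0.033.
- 1000 candidates, N = 1545: +0.087 against −0.152.

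**5. Confounders.**
- Survival setting, N = 2,000, 5:1, about 408 deaths, no true treatment effect, and four confounders with hazard ratio 1.10 per SD, each shifted by 0.5 SD between groups. Screening keeps 2.3 of the 4 on average; the estimated hazard ratio is 1.05 and the type I error 7.5%. Keeping all four gives 1.01 and 5.1%.
- Logistic setting, N = 1545 or 2,000, one confounder with log odds ratio 0.15 to 0.30 per SD. It is dropped in 0% to 46% of runs. In the worst case (N = 1545, effect masked by treatment) the mean treatment log odds ratio moves from −0.187 to −0.142, that is, from an odds ratio of e^(−0.187) = 0.83 to e^(−0.142) = 0.87.

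**The case against.** A reader might infer that the plan screens all men by univariate significance, then builds models, then cross-validates them, so that its validated performance is bound to be optimistic. The text does not say this. The order is only the order of the sentences. Guiding a model may mean choosing coding or functional form, or merging sparse categories. Cross samples may mean separate development and validation sets, with all univariate work confined to the first. This part of the objection stands, and the point is conditional for that reason.

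A reader might also infer that real confounders will be dropped. The section points the other way: it treats causal models separately and says that potential confounders are included. What it leaves open is how they are identified, directly after saying that univariate results guide multivariable modelling. The causal half is therefore a possibility, and of modest size.

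The sizes rest on assumed inputs. A short list of recently proposed biomarkers could be near 10 candidates, where the optimism is negligible. Genetic and post-genetic markers, and a platform for future ones, make longer lists plausible, but the article gives no count.

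Finally, it can be said that this is detail for a fuller plan. That would settle the matter if the article were silent. It states a rule, however, and a later plan that fixed confounders in advance and confined selection to training samples would have to narrow it.

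**Conclusion.** The concern holds in conditional form. The sentence permits univariate selection outside the validation and permits it for confounders; it prescribes neither. If selection is done once on all men, cross-validated AUC for noise rises by about 0.01 with 10 candidates, 0.05 with 50 and 0.10 with 200 at N = 2,000. If selection is repeated in each training sample, this optimism disappears. The mechanism is certain, but its size depends on the assumed p<0.05 screen and marker count. Bias in the treatment comparisons would be small in most of the settings tried and is the weaker half of the point. The wording should be changed before the models are built, because validated scores and treatment recommendations are what the study sets out to deliver.

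**What to change.** Replace the sentence on univariate results with wording such as:

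> Univariate results are descriptive. Confounders for causal models are chosen in advance on subject-matter grounds and kept regardless of univariate results. For prognostic scores, every data-driven selection step is repeated within each training sample.

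Penalised regression is one way to meet the last requirement but is optional. No new data are needed. The cost is slightly more computing and reported performance that looks less favourable than it would with a single screen on all men.

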## Methods/Design

### Study design

This is a prospective, multi-center cohort study with observational character concerning outcome. We will acquire clinical data including quality of life and lifestyle, prostate tissue specimen as well as further biological samples (blood and urine) before, during and after treatment for setup of a bio-bank.

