### Study location

We set up this study within the Canton of Zurich, Switzerland. An expansion to a national or even international study is possible and intended.

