## Discussion

This paper describes the rational, methodology and design of a prospective, multi-center cohort study within the Canton of Zurich including patients with localized prostate cancer independent of treatment finally chosen. We intend to set up a prospectively acquired clinical database including quality of life data and lifestyle factors with corresponding prostate tissue specimens (biopsy cores and/or whole organ, dependent of treatment finally chosen) and further bio-samples (blood and urine).

Based on the results we will identify treatment specific influences on quality of life and formulate appropriate treatment recommendations. Examination of biomarkers will contribute to a better understanding of the underlying biological mechanisms and will guide the development of new diagnostic and prognostic algorithms. Therefore this study will help to improve decision-making. It will help patients weighing the pros and cons of various treatment modalities and it will help physicians to inform their patients adequately.

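### Validating prognostic scores in cross samples, judged by the Brier score alone, need not reveal miscalibration at an unseen clinic; leave-one-clinic-out validation with per-clinic calibration would be a cheap improvement

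*Protocol article*

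**What the plan says.** The design is multi-centre: "This is a prospective, multi-center cohort study with observational character concerning outcome" (Study design). On the scores, the Statistical analysis section says three things:

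- Model type: "Prognostic scores will be built using either multivariate logistic regression analysis or Cox proportional hazard models".
- Validation: "Models will be validated in cross samples".
- Measure: "Calibration and discrimination of the cross-validated prognostic instruments will be assessed using the Brier Score".

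The section does not say whether the cross samples are formed by patient, clinic or period, nor whether performance is shown by clinic. It names no other validation and rules none out.

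Two other places bear on where results might be used. Study location says "An expansion to a national or even international study is possible and intended". The Discussion says that the biomarker work "will guide the development of new diagnostic and prognostic algorithms".

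**The concern.** A score used to advise an individual patient is only as good as its absolute risks. A fitted logistic model with an intercept reproduces the overall event count of the data it was fitted to. If men from every clinic are in both the fitting and the test folds, the pooled observed and expected counts therefore agree almost by construction. Suppose clinics differ in baseline risk for reasons the predictors do not capture. The score is then too high at some clinics and too low at others, and the pooled figure averages this away. The Brier score is one number that mixes calibration, discrimination and outcome variance, so it gives little warning.

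At stake is a score reported as satisfactory whose risks are materially off at the next clinic to use it. A multi-centre cohort already holds the natural test for this, namely clinics that the model has not seen.

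**Working it through.** **Inputs.** The article states no figure for score validation, so there is none to reproduce.

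- From Study sample size and duration: about 200 patients a year for ten years, 200 × 10 = 2,000. The control median is 15 years ("assumed a median survival time in the control group of 15 years"). A hazard ratio of 1.2 gives 15 × 1.2 = 18 years in the other group. Accrual lasts A = 10 years with no further follow-up.
- Implied event proportion, with exponential survival and uniform accrual: p = 1 − (1 − e^(−λA))/(λA), λ = ln 2/median. At 15 years, λA = 0.4621 and p = 1 − 0.3700/0.4621 = 0.199. At 18 years, λA = 0.3851 and p = 1 − 0.3196/0.3851 = 0.170. The 16% used in simulation A is slightly lower.
- Assumed, not in the article: number of clinics, between-clinic SD of the log-odds intercept, number of predictors, and random patient-level folds. Both simulations use logistic models.

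**Simulation A.** N = 2,000, about 16% events, 10 predictors, 6 clinics, 200 replicates. Pooled observed/expected (O/E) under random 10-fold cross-validation was 1.00 throughout.

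| Between-clinic SD | Left-out-clinic O/E, 10th–90th percentile |
|---|---|
| 0 | 0.84–1.19 |
| 0.2 | 0.74–1.31 |
| 0.4 | 0.61–1.51 |
| 0.6 | 0.48–1.70 |

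At SD 0.4 the range was 0.60–1.57 with 3 clinics and 0.59–1.47 with 10.

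*Hand check, SD 0.* Each clinic has 2,000/6 = 333 men and 333 × 0.16 ≈ 53 events; the other five have about 267. The variance of O/E is about 0.84/53.3 + 0.84/266.7 = 0.0189, so the SE is 0.137. Then 1 ± 1.28 × 0.137 gives 0.82–1.18, which agrees with the table.

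*Hand check, SD 0.4.* A clinic differs from the mean of the other five with SD 0.4 × √(6/5) = 0.438 in log-odds, or about 0.84 × 0.438 = 0.368 in log-risk. With noise, √(0.368² + 0.0189) = 0.393, and exp(±1.28 × 0.393) gives 0.60–1.65. This is slightly wider than simulated, as expected, because spread in individual risks reduces the 0.84 factor.

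**Simulation B.** 8 clinics × 250 patients, three predictors, 60 replicates. It separates the split unit from the reporting level. The middle three columns are mean absolute observed-minus-predicted risk per clinic.

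| SD | Random folds, by clinic | Clinic left out | New clinic | Brier: random / left out / new |
|---|---|---|---|---|
| 0 | 0.018 | 0.020 | 0.021 | 0.157 / 0.157 / 0.156 |
| 0.2 | 0.030 | 0.034 | 0.034 | 0.156 / 0.157 / 0.157 |
| 0.4 | 0.051 | 0.059 | 0.057 | 0.161 / 0.162 / 0.161 |
| 0.6 | 0.072 | 0.083 | 0.080 | 0.162 / 0.164 / 0.165 |

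Pooled observed-minus-predicted was 0.0001 with random folds and 0.0001 to 0.0002 with clinics left out.

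1. *Reporting level.* The pooled figure looks perfect under either split. Leaving clinics out without reporting by clinic reveals nothing in this figure.
2. *Split unit.* Tabulating random-fold predictions by clinic shows 0.0723/0.0825 = 0.88 of the left-out misfit at SD 0.6 and 0.0512/0.0585 = 0.88 at SD 0.4. Algebra agrees. With J equal clinics and the same case mix, a clinic's deviation from the overall mean is (1 − 1/J) times its deviation from the other clinics: 7/8 = 0.875 for J = 8. The split unit hides the remaining 1/J, which is 1/6 for six clinics and 1/3 for three.
3. *Brier score.* A uniform risk error d adds about d². At SD 0.4, 0.057² = 0.0032, or 2% of 0.161. At SD 0.6, 0.080² = 0.0064, or 4% of 0.165. Random folds already contain most of this, so the score moves by only about 0.003 (0.162 to 0.165) at SD 0.6.

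A separate run at SD 0.4 agreed. Left-out-clinic O/E was 0.61–1.56, random-fold O/E by clinic was 0.65–1.43, and the Brier score moved from 0.118 to 0.119.

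**The case against.** The strongest reply is that the article fixes less than the concern needs. It does not say that folds are random, that summaries are pooled, or that no further validation will follow. Splitting by clinic would fit the sentence. Fold construction is something a journal article commonly leaves to the full protocol or analysis plan. All of this stands, so the point cannot be put as an error. What remains is that the article does name a method and a single measure, and that measure barely registers clinic misfit under either split.

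The second reply is that setting pooled O/E under random folds against per-clinic O/E under left-out folds changes two things at once. That also stands. Separating them shows that reporting level does most of the work.

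The third is that every size above rests on assumed clinic differences. It stands too: at SD 0 the spread is sampling noise, and at SD 0.2 noise is still a large part of it.

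A reader might infer more, and the article does not support it:

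- *That a misfitting score will look well calibrated at any clinic.* This needs real clinic differences, random splits and pooled-only reporting together. The article states none of them.
- *That the scores are already presented as fit for outside clinics.* Study location speaks of expanding the study, and the Discussion speaks of guiding later development.
- *That intervals for treatment comparisons will be too narrow because clinic is ignored.* The section adjusts for confounders without listing them, so clinic may be among them. That is a separate matter.

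**Conclusion.** The point holds as a cheap improvement. Read in the ordinary way, the stated validation answers how the scores perform for new patients at the same clinics, and a good result would not show that absolute risks hold at a clinic left out of the fit. If the between-clinic SD were 0.4 in log-odds with six clinics, left-out-clinic O/E would typically lie between about 0.6 and 1.5, against about 0.8 to 1.2 from noise alone. The pooled ratio would read 1.00 and the Brier score would hardly move. If clinics do not differ, nothing is hidden.

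The size rests on the assumed number of clinics, SD and random folds. The direction rests only on the algebra of pooled calibration and on the Brier score being a single composite.

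**What to change.** Replace the validation sentence with:

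> Models will be validated by leaving out one clinic at a time; the observed/expected ratio and calibration slope will be reported per clinic with confidence intervals, beside the Brier score and the ordinary cross-validated result.

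Both parts are needed, because leaving clinics out without per-clinic reporting would still give a near-perfect pooled figure. Shrinking coefficients by a pooled calibration slope is not proposed: it does not correct differences in clinic intercepts, which are what was simulated. Formal pooling across clinics need not be required either, since with few clinics it would be imprecise.

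The cost is one sentence and a few lines of code, with no new data, visits or patients. The downside is that per-clinic estimates are noisy, especially with few or small clinics (about 53 events per clinic in simulation A), and reported performance may look less favourable. The confidence intervals are there so that noise is not read as misfit.
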